### Fidelity

All nurses will receive a half-day training to deliver the manualized program components, in addition to the training they already received to deliver Supportive Parenting. Nurses will be explicitly instructed, and repeatedly reminded in follow-up contact, to deliver the manualized components to mothers in the experimental group, and not to mothers in the control group. To monitor fidelity of the manualized components, and detect any possible contamination between the two groups (i.e., nurses might unwittingly offer some aspects of the components to mothers in the control group as well), nurses will complete a checklist after each home visit in which they specify to what extent and in what way the four risk factors have been targeted. This will be done for all home visits to all mothers (i.e., experimental and control group).

As an additional fidelity check, we will include a second control group, consisting of 25 mothers in one of the regions that offer Supportive Parenting, but where nurses have not yet received training in the four manualized components. This is a non-randomized group, because all participating mothers in this region will be allocated to this second control group. Mothers and nurses in this group will fill out the same questionnaires and checklists as mothers and nurses included in the main part of the study. Comparing the scores of the two control groups allows us to estimate to what extent training nurses in the use of the manualized components unwittingly impacted mothers in the control group (i.e., contamination). Should we detect contamination, as indicated by the checklists, and trends that the regular control group outperforms the non-randomized control group, this could suggest that the effects of adding manualized components are larger than measured in this study.

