**Methods:**

We will conduct a randomized controlled trial among 398 mothers enrolled in a Dutch home visiting program targeting families at risk for child maltreatment. Mothers in the experimental group will receive the manualized components in two consecutive home visits, while mothers in the control group will receive regular home visits (care as usual). Mothers will fill out questionnaires at four time points: before and after each of the two home visits. Outcome variables include the four targeted risk factors parental self-efficacy, perceived stress, parental anger, and (recognition of) post-traumatic stress symptoms, as well as parenting practices (e.g., rejection and affection), and risk for child maltreatment.

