## Methods/design

### Design

We will conduct a randomized controlled trial in the context of an existing Dutch home visiting program aimed at the prevention of child maltreatment (Supportive Parenting, in Dutch “*Stevig Ouderschap*” [54]). Mothers will be randomly assigned to receive either two consecutive home visits that include the additional manualized components (i.e., manualized home visiting), or to receive standard home visits (i.e., care as usual) with a 1:1 allocation using a computerized random number generator.

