**Fig. 1 Fig1:**
[figure not shown]
Participant flow chart

This study will follow mothers over the course of any two consecutive Supportive Parenting home visits, which will be named home visit A and B in this study. Home visits tend to be about three months apart from each other, but this may vary in clinical practice. Mothers will fill out online questionnaires four times; one to two weeks before home visit A visit (T1), one to two weeks after home visit A (T2), one to two weeks before home visit B (T3), and one to two weeks after home visit B (T4). We offer mothers assistance in filling out the questionnaires by phone. We will send text messages by phone to remind mothers to fill out the questionnaires. Mothers receive a compensation of 5 euros for each questionnaire they fill out, and an additional 5 euros if they fill out all the questionnaires.

Mothers in the experimental group will receive two Supportive Parenting home visits (A and B) in which nurses will deliver the manualized components. All four components will be delivered in both home visits. Mothers in the control group will receive two regular Supportive Parenting home visits that do not include the manualized components. As we do not expect any adverse effects from these components, we did not set any criteria to discontinue the components. There are no restrictions for mothers to seek any additional help, but mothers are asked to report it if they do so.

This study has been approved by the Ethics Review Board of the Faculty of Social and Behavioral Sciences of the University of Amsterdam (ref nr: 2018-CDE-9258) and the trial has been registered in the Dutch Trial Register (NL8005). Any meaningful changes will be reviewed by the Ethics Review Board of the Faculty of Social and Behavioral Sciences of the University of Amsterdam and will be reported in the effect paper.

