### Sample size calculation

As we will compare two active conditions, we expect to find relatively small effects. More specifically, we expect moderate effects on the targeted risk factors (i.e., our more proximal outcome measure) and a small effect on mothers’ risk for child maltreatment (i.e., our more distal outcome measure). Previous additive studies (i.e., studies in which effects of an intervention are compared to effects of the same intervention with one or more additional components) also demonstrated small to moderate average effect sizes for interventions with added components [77]. Our sample of *N =* 398, with two groups and one-sided tests at α = .05 provide us with a power (1 – β) of .80 to detect effects of *d* = .25 [78]. Following the guidelines of Fritz and MacKinnon [79], our sample size will also allow for sufficient power to detect mediation effects when using mediation analyses based on bootstrapping.

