### Analyses

Prior to analyzing the data, missing data will be handled with multiple imputation. To test whether adding manualized components ameliorates four risk factors (i.e., low parental self-efficacy, high levels of perceived stress, parental anger, and post-traumatic stress symptoms), improves parenting practices, and reduces risk for child maltreatment, we will conduct multivariate analyses of covariance (MANCOVA) and an analysis of covariance (ANCOVA) respectively, with baseline scores (T1) as the covariates, with data of T2, T3, and T4 for the risk factors and data of T4 for parenting practices and risk for child maltreatment as dependent variables.

To test whether amelioration of the targeted risk factors by the added components explains (i.e., mediates) reduced risk for child maltreatment we will conduct a mediation analysis using the PROCESS Macro in SPSS [80]. This macro computes 95% confidence intervals of the indirect effects based on 1000 bootstrap samples. Intervals that do not include 0 indicate a mediation effect.

To test who benefits most from the manualized components we will test whether condition × child, maternal, or family characteristic interaction effects predict ameliorated risk factors and reduced risk for child maltreatment. Putative moderators include mothers’ baseline levels of each of the four risk factors (maternal characteristics), children’s temperament (child characteristic), and the number of life events in the past year and during the study (family characteristic).

We will conduct interim descriptive analyses for our progress annual reports for the study funder. However, no interim analyses that answer the research questions of this study will be conducted. The full protocol, anonymized dataset, and the statistical code that will be used in this study will be available upon motivated request after publication of the results in a peer-reviewed paper.

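### The planned models have no nurse term although trained nurses deliver the components and serve both arms: a small loss of precision, and standard errors too small only if the effect varies between nurses

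*Protocol article*

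**What the plan says.** Mothers are randomised individually, after consent, "with a 1:1 allocation using a computerized random number generator" (Design; Procedure). No stratification by nurse or centre is mentioned.

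Nurses deliver the components (Added Manualized components). All nurses in the randomised part are trained, and they are told "to deliver the manualized components to mothers in the experimental group, and not to mothers in the control group" (Fidelity). They complete a checklist after every visit in both arms. The article treats the shared nurse as a contamination risk, watched through these checklists and a second, non-randomised control group.

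The Analyses section compares the arms by MANCOVA and ANCOVA "with baseline scores (T1) as the covariates". The dependent variables are T2, T3 and T4 for the risk factors, and T4 for parenting practices and maltreatment risk. No nurse or centre term is named. The Sample size calculation is a plain two-group calculation, "with two groups and one-sided tests at α = .05", with power .80 "to detect effects of *d* = .25".

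A mother may join for "any two consecutive Supportive Parenting home visits" (Procedure), so child age and visit number at entry differ between mothers.

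**The concern.** Mothers visited by one nurse may have correlated outcomes, and nurses may differ in how well they deliver the components. Much is left to the nurse: which parenting practices to praise, how to encourage the daily relaxation exercise, how to discuss anger triggers, and how to motivate a mother to seek help. A half-day of training and a fidelity checklist suggest that delivery is expected to vary.

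The stated models leave this structure out. Two things are at stake. Variance common to a nurse's mothers stays in the error term, which costs precision. If the effect itself differs between nurses, the reported standard error leaves out part of the uncertainty about the average effect. That part matters because the Discussion draws conclusions for the programme and for prevention programmes generally, not only for the nurses who took part.

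**Working it through.** **Inputs from the article.** N = 398, so 199 per arm; one-sided α = .05; d = .25; power .80; individual 1:1 allocation.

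**Inputs that are assumed.** The article does not give the number of nurses J, mothers per nurse m = 398/J, the nurse share of the variance ρ, or the between-nurse variance of the effect τ² (outcome SD = 1). Ranges used: J = 20-60, ρ = .05-.10, τ² = .02-.10. In terms of SD, τ runs from √.02 = .14 to √.10 = .32.

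**1. The stated power.** With independent mothers the variance of the difference is 4/398 = .01005, so SE = .1002. Power = Φ(.25/.1002 − 1.645) = .802, and .801 with the noncentral t. The stated .80 is reproduced as a one-sided test with no allowance for nurses.

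**2. A nurse effect common to both arms (τ² = 0).** With arms balanced within nurse, the variance becomes 4(1 − ρ)/398.
- ρ = .05: true SE / ordinary SE = √.95 = .975; power with a nurse term .820.
- ρ = .10: ratio √.90 = .949; power .837.

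Under simple randomisation that ignores nurse, a simulation (10,000 trials per scenario, 4, 10 or 20 mothers per nurse, unadjusted two-sample test) gave ratios of .99-1.01 and one-sided errors of .046-.052. The Monte Carlo standard error is √(.05 × .95/10,000) = .002. The ordinary standard error is therefore about right, but the interval is wider than it need be.

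**3. An effect that varies between nurses.** The approximate variance is 4/398 + τ²/J. The inflation is VIF = 1 + (τ²/J)/.01005, and the one-sided error is 1 − Φ(1.645/√VIF).
- J = 60, τ² = .02: VIF = 1 + .00033/.01005 = 1.03; error .053.
- J = 40, τ² = .05: VIF = 1 + .00125/.01005 = 1.12; error .060.
- J = 20, τ² = .10: VIF = 1 + .00500/.01005 = 1.50; error .089.

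The simulation with ρ = .05 and simple randomisation agrees (true SE / ordinary SE; one-sided error):

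| Mothers per nurse | τ² = .02 | τ² = .05 | τ² = .10 |
|---|---|---|---|
| 4 | 1.00; .049 | 1.02; .053 | 1.03; .053 |
| 10 | 1.02; .054 | 1.05; .058 | 1.11; .068 |
| 20 | 1.05; .059 | 1.11; .069 | 1.21; .089 |

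Power with the correct standard error (ρ = .05, balanced within nurse) is .80 at m = 4 and τ² = .05, .78 at m = 10 and τ² = .05, and .67 at m = 20 and τ² = .10.

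**The case against.** The strongest reply is that individual randomisation deals with the nurse effect. A shared effect largely cancels from the arm contrast, and step 2 bears this out. A reader might infer from the shared nurses that the standard errors are wrong as a matter of fact, or that the design effect of a cluster-randomised trial applies. The article supports neither, because nurses are crossed with arm and not nested in it.

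The harmful route, variation of the effect, rests wholly on assumed values. The upper end needs a between-nurse SD of .32, larger than the design effect of .25. If the components do nothing for any mother, τ² is zero and the inflation vanishes. This also stands. The inflation concerns a zero average effect made up of differing nurse-specific effects, and it concerns power and interval width when the average is not zero.

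That every nurse sees mothers in both arms is likewise an inference. A nurse with few mothers may see one arm only. The text shows only that the pool of nurses is shared.

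Finally, an article condenses, and provider effects are often left to an analysis plan. Here, though, the article names the model family and its covariates, and a nurse term would alter that stated model. The contamination measures answer a different question and leave the model as it is.

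**Conclusion.** The point holds in a limited form. The stated models take no account of the nurses who deliver the intervention and serve both arms. The certain cost is minor: if nurses account for 5-10% of the variance and arms are balanced within nurse, power of about .80 could have been .82-.84. The possible cost is larger but cannot be sized from the article. With 20-60 nurses and τ² of .02-.10, the one-sided error is .053-.089, and it is near .05 at about four mothers per nurse.

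A two-sided error for the same worst corner would be .109, but the sample size section plans one-sided tests, so .089 is the relevant upper figure. The calculations use a single outcome without T1 adjustment, so they indicate the order of size and do not predict the trial's own error rate.

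**What to change.** Keep the planned outcomes and times (T2, T3 and T4 for the risk factors; T4 for parenting practices and maltreatment risk). Analyse them with mixed models containing T1, condition and a random nurse intercept. The intercept recovers precision but does not protect against an effect that varies between nurses. For that, pre-specify one sensitivity analysis: either a nurse-by-condition random slope, or nurse-clustered standard errors with a small-sample correction. Its form should not depend on the estimated slope variance. Report the number of nurses and the number of mothers per nurse and arm.

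The cost is a change of analysis wording. Nurses complete a checklist for every visit in both arms, so nurse identity should be linkable, and recruitment is still under way. The downside is that intervals may widen if delivery varies between nurses.

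Separately and optionally, the visit number of home visit A or child age at T1 could be added as a baseline covariate, since mothers enter at different visits. This is for precision only and corrects no error.

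### Comparing about 199 regular controls with 25 non-randomised mothers from one region cannot estimate contamination, and score trends from it should not support reading the effect as larger than measured

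*Protocol article*

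**What the plan says.** All of this is in the Fidelity section of the protocol article. Nurses are told to deliver the components only in the experimental group. To monitor this, "nurses will complete a checklist after each home visit in which they specify to what extent and in what way" each risk factor was addressed, for every visit in both arms.

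As a further check, "we will include a second control group, consisting of 25 mothers in one of the regions that offer Supportive Parenting", in a place where nurses have not yet been trained. The article is open about the allocation: "This is a non-randomized group, because all participating mothers in this region will be allocated to this second control group".

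Two statements then say what this group is for. The first carries no condition: "Comparing the scores of the two control groups allows us to estimate to what extent training nurses in the use of the manualized components" affected the control mothers. The second is an interpretive rule with two conditions: "Should we detect contamination, as indicated by the checklists, and trends that the regular control group outperforms the non-randomized control group". If both are met, "this could suggest that the effects of adding manualized components are larger than measured in this study". The half of the rule examined here, together with its consequence, reads "trends that the regular control group outperforms the non-randomized control group, this could suggest that the effects of adding manualized components are larger".

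The section does not say what counts as a trend, or on which outcomes and time points. It does not mention region as another explanation, and it gives no reading for a null or opposite pattern. The Analyses section does not use the second control group in any effect analysis.

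**The concern.** Contamination is a real threat here, because the same trained nurses see mothers in both arms. If controls receive parts of the components, the randomised contrast shrinks. That reasoning is sound. The question is whether the 25 mothers can show that it happened and that it affected outcomes.

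Two things suggest that they cannot. The group is identical with one region, so any difference from the regular controls mixes nurse training with region, nurse team and case mix. It is also very small for the size of difference that matters.

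What is at stake is the interpretation of a null or small randomised result. The article sets out in advance a route by which such a result could be described as an underestimate, and part of the evidence for that would be noise or regional difference.

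**Working it through.** **Inputs.** From the article: N = 398 with 1:1 allocation, so 398/2 = 199 regular controls; 25 mothers in the second control group; one-sided α = .05, power .80 and d = .25 (Sample size calculation). Assumed, because the article does not give them: SD = 1, no dropout, independent observations, a correlation of 0.5 to 0.7 between T1 and outcome, and a correlation of 0 to 0.5 between the four primary outcomes.

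**The article's own figure.** n per arm = 2 × (1.645 + 0.842)² / 0.25² = 198, or 396 in total. With 199 per arm, one-sided power at d = .25 is 0.80. The stated power reproduces.

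**Precision of the contamination comparison.**
- SE = √(1/199 + 1/25) = 0.212 SD.
- 95% half-width = 1.96 × 0.212 = 0.42 SD.
- With T1 adjustment, SE is multiplied by √(1 − r²). The half-width is 0.36 at r = 0.5 and 0.30 at r = 0.7.
- Difference detectable with 80% one-sided power = (1.645 + 0.842) × 0.212 = 0.53 SD (0.46 to 0.38 with T1 adjustment).

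Clustering by nurse team would widen these intervals.

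**Power, one-sided α = .05.** Power = Φ(d/SE − 1.645).

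| True difference between control groups | Unadjusted | T1-adjusted, r = 0.5 to 0.7 |
|---|---|---|
| 0.125 SD | 15% | 17% to 21% |
| 0.25 SD | 32% | 39% to 50% |

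**What a trend tells us.** If trend means direction only, P(favours regular controls) = Φ(d/SE), unadjusted:
- No true and no regional difference: 0.50 per outcome.
- True difference of 0.125: 0.72. True difference of 0.25: 0.88.
- No contamination but an assumed regional difference of 0.2 SD: 0.83 or 0.17, depending on its sign.

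A regional difference of 0.2 SD thus moves the direction about as far as contamination would. With no true or regional difference, at least one of the four primary outcomes points the favourable way with probability 0.94 if they are independent and 0.80 at correlation 0.5. If trend instead means one-sided p < .10, the figures are 0.10 per outcome and 0.34 to 0.26 for any of four. Table 1 leaves many places to look: 4 primary outcomes × 3 post-baseline times = 12, plus four parenting scores and one risk score at T4, 17 in all.

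**Confounding.** All participating mothers in the region enter the second group. No mother there has a trained nurse, and no regular control comes from there. T1 adjustment removes measured baseline differences in the score. It does not remove differences between regions in usual care or in change over time.

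**The case against.** The strongest defence is that the rule has two conditions. Contamination must first appear on the checklists, which are completed for every visit in both arms. A reader who starts the sentence at the word trends might infer that a trend alone is enough. It is not. The 0.80 to 0.94 figures are therefore at most upper bounds on a false trigger, and only if trend means direction on any one outcome.

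A reader might also infer that d = .25 caps how large contamination can be. The article does not say so. In the Sample size calculation .25 is the detectable effect, and moderate effects are expected on the targeted risk factors. If moderate is taken as 0.5 (an assumption), full leakage would be seen with power of about 76% unadjusted and 86% to 95% with T1 adjustment. Leakage of half of it is again a difference of 0.25, with 32% unadjusted.

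The defence can add that the wording is hedged, that the group is presented as an additional fidelity check and called non-randomised, that contamination does bias towards zero, and that a definition of trend may sit in a fuller document.

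Most of this stands. It limits the point to interpretation. It does not rescue the unconditional statement that the score comparison estimates contamination, and no definition of trend removes the regional confounding or narrows the interval. The checklist condition is also not clean. It records how far the risk factors were addressed, and usual care is flexible and supports parenting skills (Intervention section), so some entries in the control arm could reflect ordinary care.

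**Conclusion.** The point holds as one of interpretation. The comparison of about 199 with 25 cannot estimate contamination: region and nurse team are fully confounded with training, and the interval of ±0.42 SD (±0.30 to 0.36 adjusted) has a half-width larger than the d = .25 for which the trial is powered. An undefined trend therefore adds little to the checklist evidence, and the only reading written down is that the effect is larger.

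A reader might go further and infer that the rule can inflate the trial's result. The documents do not support that. The second control group enters no planned test or estimate, the reading needs checklist evidence as well, and it is worded as a possibility.

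The change is worth making because it governs what may be said after a null or small result. The figures rest on SD = 1, no dropout, independent observations and the assumed correlations. Dropout or clustering would make precision worse.

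**What to change.** In the Fidelity section:

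1. Replace the claim of estimation with a descriptive aim.
2. Report the T1-adjusted difference between the two control groups with its 95% interval, and name region, nurse team and case mix as alternative explanations.
3. State how the other patterns will be read. A null difference with an interval this wide does not exclude contamination, and an opposite difference is open to the same regional explanation.
4. Remove trends as support for a larger effect. Base any statement on contamination on the nurse checklists in both arms, word it as possible attenuation, and keep the as-randomised result as the conclusion.

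The cost is wording. The 25 mothers, the questionnaires, the checklists and every test in the Analyses section stay as they are. Recruitment is ongoing according to Study status, so the change can precede the results. The only loss is one favourable interpretation.

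A sensitivity analysis using randomised condition as an instrument for components delivered is optional. It would rely on unblinded nurse reports and on an exposure that the checklists do not clearly define, so it is not part of the required change.
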